#### Secondary analysis

The sample size calculation was based on the primary outcome, and the main conclusions of the study will be drawn from this analysis. Secondary outcomes will be considered exploratory.

To address the issue of multiple comparisons, statistical correction procedures will be applied as appropriate. In multivariable models, the commonly used rule of thumb of one predictor variable per ten participants will be followed to reduce the risk of overfitting.^49^

#### Clinical outcomes

The longitudinal evolution of each secondary outcome (COMI, ODI, VAS, HADS, FABQ, PCS) at weeks 4, 12 and 24 will be compared between groups using a mixed-effects regression model.

A random effect for subjects and fixed effects for time and group will be included in the model. To assess potential differences in outcome trajectories between groups over time, an interaction term between time and group will be specified and evaluated using a likelihood ratio test. Intention-to-treat approach will be applied.

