### Objectives and hypothesis

The primary objective of this study is to compare the effectiveness of repeated nine sessions of anodal tDCS targeting the DLPFC combined with an intensive exercise programme to nine sessions of sham tDCS combined with the same exercise programme. The comparison will focus on pain intensity and the multidimensional impact of pain in patients with CLBP immediately after the intervention.

The secondary objectives are to assess the effects of repeated sessions of tDCS over the DLPFC combined with an exercise programme on:

Pain, disability and psychological factors:Pain intensity, multidimensional impact of pain, functional disability and psychological outcomes (including fear-avoidance beliefs, catastrophising, anxiety and depression) immediately after the intervention (week 4), with follow-ups at 12 and 24 weeks.Functional brain connectivity:Changes in functional resting-state brain connectivity as evaluated by electroencephalography (EEG) over the DLPFC and its associated neural networks, between baseline and immediately after the intervention (week 4).Neuromuscular function of the erector spinae:The restoration of the flexion–relaxation phenomenon (FRP) in the erector spinae during forward bending was assessed immediately after the intervention (week 4).

We hypothesise that anodal tDCS targeting the DLPFC, combined with an intensive exercise programme, will lead to greater improvements in all clinically measured outcomes compared with sham tDCS combined with the same exercise programme, both immediately after the intervention (week 4) and at the 12- and 24-week follow-ups. Regarding functional brain connectivity, we hypothesise an increase in DLPFC connectivity with associated areas, and for the neuromuscular function, a restoration of FRP in the erector spinae muscles. Further, the magnitude of these neurophysiological changes will correlate with clinical improvements.

This protocol is version 1.0, dated 12 February 2026.

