### Sample size calculation

An a priori sample size calculation was conducted using G*Power software (V.3.1.9.4). The estimation was based on the Minimal Clinically Important Improvement for the COMI, considered the primary outcome measure, with a reference value of 2.6 points.^47^ This endpoint was defined as the difference in COMI scores between baseline and immediately postintervention (week 4).

The expected SD of the COMI score in both groups was conservatively estimated at 3, based on a previous study^48^ and expert clinical judgement. With a significance level (α) of 0.05 (two-tailed) and a desired statistical power of 80% (1−β), the required sample size was calculated to be 22 participants per group to detect a clinically meaningful between-group difference.

To account for an anticipated dropout rate of 10%, the recruitment target was adjusted to 24 participants per group. Therefore, a total of 48 participants will be enrolled in this trial.

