### Statistical analysis

All primary and secondary outcome measures will be analysed according to the intention-to-treat principle. A two-tailed superiority testing approach will be applied, with the level of statistical significance set at α=0.05 (p<0.05).

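### The only test named for the clinical secondary outcomes, a time-by-group interaction over weeks 4, 12 and 24, cannot detect a benefit that stays constant over those visits

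*Protocol article*

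**What the plan says.** The section on clinical outcomes under Secondary analysis states: "The longitudinal evolution of each secondary outcome (COMI, ODI, VAS, HADS, FABQ, PCS) at weeks 4, 12 and 24 will be compared between groups". The model has a random subject effect and fixed effects for time and group. For differences in trajectory, "an interaction term between time and group will be specified and evaluated using a likelihood ratio test". No other test is named. The group term is in the model, but the section specifies no test of it and no contrast at a given visit. Baseline appears neither as a time level nor as a covariate.

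Three other places bear on this:
- Objectives and hypothesis expects greater improvement with active stimulation "both immediately after the intervention (week 4) and at the 12- and 24-week follow-ups".
- The Secondary outcomes section defines these outcomes as differences that involve baseline, and Table 1 schedules all the scales at baseline.
- The opening of Statistical analysis covers primary and secondary outcomes alike: "A two-tailed superiority testing approach will be applied", at the 0.05 level. The Secondary analysis section then calls the secondary outcomes exploratory.

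**The concern.** The objective is whether the groups differ at weeks 4, 12 and 24. An interaction test on those same three visits answers another question: whether the difference at week 4 is the same as at weeks 12 and 24. Once stimulation has ended, a benefit that is already present at week 4 and is maintained is a natural form of success, and under it the interaction is zero.

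This model is the only between-group analysis described for disability, pain, anxiety and depression, fear-avoidance and catastrophising, and for every week-12 and week-24 result. If the named test is the one relied on, a maintained benefit would leave no trace in it, while a benefit that wears off often would.

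**Working it through.** **Inputs.** From Sample size calculation: a COMI difference "with a reference value of 2.6 points"; "The expected SD of the COMI score in both groups was conservatively estimated at 3"; 22 evaluable and 24 recruited per group. From Statistical analysis: two-sided α = 0.05. Assumed, because the article does not give them: SD 3 at every visit, and a within-subject correlation ρ of 0.3, 0.5 or 0.7 (equal between all visits).

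**The plan's own figure.** For the primary t-test the noncentrality is 2.6 / (3 × √(2/22)) = 2.6 / 0.905 = 2.87. The noncentral t gives 80.2% power at 22 per group and 78.2% at 21, so the stated 22 is reproduced. The article states no power for the interaction test.

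**Why a constant effect is invisible.** Write the group difference at visit t as δₜ = γ + θₜ, where γ is the group term and θₜ the interaction. If δₜ = δ at all three visits, then γ = δ and every θₜ = 0. For n per group, the noncentrality of the interaction test is

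λ = (n/2) × Σ(δₜ − δ̄)² / [σ²(1 − ρ)].

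- Constant 2.6, 2.6, 2.6: the sum is 0, so λ = 0 whatever the effect size, SD or correlation.
- Fading 2.6, 1.3, 0: the sum is 1.3² + 0 + 1.3² = 3.38. At ρ = 0.5, λ = 11 × 3.38 / 4.5 = 8.26.
- Baseline added as a fourth level, 0, 2.6, 2.6, 2.6: the mean is 1.95 and the sum is 1.95² + 3 × 0.65² = 5.07. At ρ = 0.5, λ = 11 × 5.07 / 4.5 = 12.39.

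Taking change from baseline as the response at the three visits does not help. A constant shift in change scores also goes into the group term.

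**Average group difference on the same three visits.** SE = 3 × √((1 + 2ρ)/3) × √(2/22). At ρ = 0.5 this is 3 × 0.816 × 0.302 = 0.739, and 2.6 / 0.739 = 3.52.

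**Simulated rejection rates**, 22 per group, 20,000 trials per setting, maximum-likelihood test with a random intercept:

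| Test and true pattern | ρ = 0.3 | ρ = 0.5 | ρ = 0.7 |
|---|---|---|---|
| Interaction, 3 visits, no effect | 5.5% | 5.7% | 5.7% |
| Interaction, 3 visits, constant 2.6 | 5.9% | 5.5% | 5.8% |
| Average group difference, 3 visits, constant 2.6 | 97% | 93% | 88% |
| Interaction, 3 visits, fading 2.6, 1.3, 0 | 59% | 74% | 92% |
| Interaction, baseline as fourth level, then constant 2.6 | 71% | 86% | 98% |

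The excess over 5% in the first two rows comes from the chi-square approximation in a small sample; the F version gives 4.7–5.2%. With 24 per group the constant-effect row is 5.5–5.7%. A standard mixed-model routine (200 trials, ρ = 0.5, 22 per group) gave 4.5% for the constant effect on three visits and 86.5% with baseline as a fourth level.

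**The case against.** The strongest reply is that the article does not clearly commit to the three-visit model. It speaks of evolution and trajectories, the Secondary outcomes section defines the outcomes relative to baseline, and Study design lists four assessment points including baseline. With baseline as a time level, the interaction is a usual test of differential change and has reasonable power. This stands in part: the reading is possible. But the analysis section lists only the three later visits, and the two readings can lead to opposite conclusions from the same data. Even with baseline included, the test is an omnibus one over three degrees of freedom. It does not locate a difference at week 4, 12 or 24.

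A reader might go further and infer that the plan will report a lasting benefit as no difference. The article does not say so. It limits the interaction test to assessing trajectories, keeps a group term in the model, and nowhere makes a null interaction the decision rule. A reader might also infer that the hypothesis requires an equal benefit at every visit. It predicts benefit at each visit, not equality, and a benefit that grows or wanes gives a non-zero interaction. Nor is a significant interaction under a fading effect a false result, since the groups then do differ at some visits.

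A condensed article may leave contrasts to an analysis plan that is not shown. That answers a complaint about missing detail. It does not answer the fact that the visits and the test that are stated do not fit the objective together.

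**Conclusion.** The point holds as a mismatch between the stated test and the stated question, of moderate severity. That the literal three-visit interaction test rejects only at its null rate under a constant effect is algebra and rests on no assumed SD or correlation. The sizes for the comparison tests do rest on assumptions: the COMI planning values, SD 3 at each visit, an equal correlation between visits, and no missing data. They do not carry over to the other scales, for which the article gives no SD or target difference.

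The consequence is confined to the secondary and follow-up results, which the article labels exploratory. The main conclusion comes from the week-4 COMI comparison, which this does not touch.

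**What to change.** Reword the paragraph on clinical outcomes in three respects:

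1. State how baseline enters: as a covariate with weeks 4, 12 and 24 as the response visits, or as a fourth visit with a common baseline mean in both groups.
2. Make the estimated group difference with its 95% CI at each of weeks 4, 12 and 24 the reported result for each scale.
3. Keep the interaction test only to describe whether the effect changes over time.

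The cost is wording. The model family and the data are unchanged, and baseline is already collected on every scale. Because the statisticians are blinded to allocation, the change can be made credibly if it is dated before unblinding.

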#### Neurophysiological outcome

To determine neurophysiological differences between treatment groups (stimulation vs sham), unpaired pseudo-t-tests or their non-parametric equivalents will be conducted, depending on the distribution of the EEG variables of interest. EEG parameters will be analysed both on a voxelwise basis and within predefined regions of interest, with or without correction for multiple comparisons.

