**Methods and analysis:**

This is a single-centre, triple-blinded, parallel-group randomised controlled trial. 48 participants with CLBP will be randomly assigned to receive either anodal tDCS over the left PFC combined with exercises, or sham tDCS combined with the same exercise programme, over nine sessions during a 3-week period. The primary outcome is the change in the multidimensional impact of CLBP, assessed using the Core Outcome Measures Index, from baseline to postintervention (week 4). Secondary outcomes include pain intensity, disability, psychological factors (fear-avoidance beliefs, catastrophising, anxiety, depression), measured at baseline, postintervention and at 12- and 24-week follow-up. Functional brain connectivity via electroencephalography and neuromuscular function of the erector spinae (flexion–relaxation phenomenon) will be measured at baseline and postintervention.

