#### Neurophysiological outcome

Spontaneous activity in a task-free state will be assessed using a 10-min resting-state EEG.

EEG data will be continuously acquired at 512 Hz using an Active II EEG system (Biosemi, Amsterdam) with 128 pre-amplified (active) EEG channels with standard 10–20 configuration. Participants will be asked to keep their eyes closed and remain relaxed yet awake. Epochs showing artefacts or reduced vigilance were removed following visual inspection. From the remaining data, 5 min free of artefacts were re-referenced to the common average. Source-level functional connectivity (FC) will be computed in MATLAB (The MathWorks, Natick, Massachusetts, USA) using the open-source NUTMEG toolbox and its Functional Connectivity Mapping module, as previously described. Lead fields on a 10 mm grid will be generated with a boundary element model derived from an individual template 3D T1-weighted MRI (Helsinki BEM Library) via the NUTMEG plugin. Artifact-free EEG epochs will be band-pass filtered between 1 and 20 Hz using a zero-phase elliptic filter and projected to grey-matter voxels with an adaptive spatial filter (scalar minimum-variance beamformer).

Connectivity metrics will be computed separately in seven canonical bands—delta (1–3 Hz), low theta (4–5 Hz), high theta (6–7 Hz), low alpha (8–10 Hz), high alpha (11–12 Hz), low beta (13–16 Hz) and high beta (17–20 Hz). Because between-subject differences in synchronisation magnitude can reflect variations in signal-to-noise ratio, we will normalise each participant’s connectivity map within band by subtracting the subject’s mean Weighted Node Degree (WND) across all cortical voxels and dividing by the corresponding SD, yielding voxelwise z-score maps. The z-maps will then be spatially normalised to canonical MNI space using SPM8 functions (http://www.fil.ion.ucl.ac.uk/spm/software/spm8/).

Relationships between the clinical variables and NIBS-induced changes in effective connectivity/FC will be analysed with Pearson correlations and corrected with a false discovery rate of 5%.

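### The between-group EEG test does not say whether week-4 values or changes are compared, and it leaves the scheduled baseline EEG unused as a covariate; the cost is precision in an exploratory outcome, not bias

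*Protocol article*

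**What the plan says.** All references are to the protocol article.

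- **Objectives and hypothesis** sets the EEG objective as "Changes in functional resting-state brain connectivity as evaluated by electroencephalography (EEG) over the DLPFC and its associated neural networks, between baseline and immediately after" the intervention at week 4. On direction it says "we hypothesise an increase in DLPFC connectivity with associated areas".
- **Abstract (Methods and analysis) and Table 1** schedule the EEG twice, at baseline and at week 4. The abstract says that EEG connectivity and neuromuscular function "will be measured at baseline and postintervention".
- **Outcomes, Neurophysiological outcome** uses change in one analysis, the correlations: "Relationships between the clinical variables and NIBS-induced changes in effective connectivity/FC will be analysed with Pearson correlations".
- **Statistical analysis, Neurophysiological outcome** is the only place that states the between-group EEG test: "To determine neurophysiological differences between treatment groups (stimulation vs sham), unpaired pseudo-t-tests or their non-parametric equivalents will be conducted". It continues: "EEG parameters will be analysed both on a voxelwise basis and within predefined regions of interest, with or without correction for multiple comparisons". No visit, change score, baseline covariate or group-by-time term appears there.
- **Primary analysis**, by contrast, names the baseline to week-4 change in COMI as the tested variable. **Clinical outcomes** specifies a time-by-group interaction.
- **Secondary analysis** declares the secondary outcomes exploratory.

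**The concern.** The objective is a change, but the test is described only as an unpaired comparison of EEG parameters between arms. Two analyses fit that description: a comparison of week-4 maps, and a comparison of change maps. The other sections do not settle the matter by analogy. COMI is tested as a change, the clinical outcomes use a longitudinal model, and the flexion–relaxation ratio is given a paired before-after test.

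Neither reading adjusts for baseline. With about 22 evaluable participants per arm, the efficiency of the test matters, and a baseline measurement of the same quantity is already scheduled. The Discussion relies on the EEG data to help explain how the intervention works, and this test is the randomised EEG comparison behind that aim. At stake are the power of that comparison and whether its result depends on a choice that the text leaves open.

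**Working it through.** **1. The plan's own figure.** The sample size section uses a COMI difference of 2.6, SD 3, two-sided α = 0.05 and 80% power. The standardised difference is 2.6/3 = 0.867. The exact two-sample t calculation gives n = 21.9, so 22 per arm, with power 80.2% at 22. The stated 22 reproduces. The document gives no power statement for EEG.

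**2. Inputs for the EEG comparison.**
- From the document: 22 evaluable per arm (24 recruited; 24 × 0.9 = 21.6), 1:1 allocation, two-sided 5%.
- Assumed: equal between-participant SD at the two visits, taken as the unit; one voxel or region, without multiplicity correction; correlation r between a participant's baseline and week-4 values of 0.3 to 0.8.

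**3. Formulas.** The standard error of the arm difference is √(2/22 × v), where v is
- 1 for week 4 only (42 df),
- 2(1 − r) for change (42 df),
- 1 − r² for week 4 adjusted for baseline (41 df).

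The detectable difference is the value at which the noncentral t gives 80% power.

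**4. Results.**

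| r | v, week 4 only | v, change | v, adjusted | Detectable, week 4 only | Detectable, change | Detectable, adjusted |
|---|---|---|---|---|---|---|
| 0.3 | 1 | 1.40 | 0.91 | 0.86 SD | 1.02 SD | 0.83 SD |
| 0.5 | 1 | 1.00 | 0.75 | 0.86 SD | 0.86 SD | 0.75 SD |
| 0.7 | 1 | 0.60 | 0.51 | 0.86 SD | 0.67 SD | 0.62 SD |
| 0.8 | 1 | 0.40 | 0.36 | 0.86 SD | 0.55 SD | 0.52 SD |

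Against week 4 only, adjustment cuts the variance by 9%, 25%, 49% and 64%. At r = 0.5 this is worth as much as raising the unadjusted comparison from 22 to 22/0.75 ≈ 29 per arm. As an example in power terms, at an assumed effect of 0.5 SD and r = 0.7, power is 37% (week 4 only), 55% (change) and 62% (adjusted).

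**5. Why adjustment and not just change.** 1 − r² = (1 − r)(1 + r) never exceeds 1, and never exceeds 2(1 − r) because 1 + r ≤ 2. Change is less precise than week 4 only whenever 2(1 − r) > 1, that is, r < 0.5. Inserting the word change alone could therefore lose precision. Estimating the baseline slope adds a small cost that the formula leaves out, roughly 1/(44 − 4) = 2.5% of the variance. That is about 1.2% on the detectable difference (√1.025 = 1.012), too little to reverse the gain even at r = 0.3 (0.91 × 1.025 = 0.93).

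**6. Does the choice of variable matter?** In simulation (4,000 trials per setting, 22 per arm, effect 0.5 SD), the week-4 and change tests disagreed on significance in 29%, 31% and 40% of trials at r = 0.3, 0.5 and 0.7. With no effect, the error rate of each of the three tests, used alone, was about 5%.

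**The case against.** The strongest reply is that this is silence in a condensed article. Unpaired describes two independent arms and does not rule out change maps as the input. Given the objective and the correlations, change is the natural reading, and the exact input variable is the kind of detail a statistical analysis plan supplies. Part of this stands: the text does not contradict itself outright, and the change reading is plausible. But the article does fix the test, and an unadjusted two-sample test omits the baseline covariate under either reading. A better use of data already scheduled can be recommended without calling the detail missing.

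A reader might also infer more than the documents support:

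- **That a week-4 comparison tests a different quantity or is biased.** It does not. With 1:1 randomisation the expected week-4 difference and the expected difference in change are the same.
- **That chance baseline differences pass straight into the result.** With equal SDs, a baseline difference d moves the expected week-4 difference by r × d, half of d at r = 0.5, and the standard error already covers this.
- **That the error rate is inflated.** A figure near 9% arises only if an analyst runs both versions and keeps the favourable one. No such choice is planned, and the analysts are to be blinded to allocation.
- **That every participant will have a usable baseline EEG.** It is scheduled for all, but five artefact-free minutes are needed, so some may be lost.

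It is also fair to say that adjustment adds little to a change analysis when r is high (0.67 to 0.62 SD at r = 0.7; 0.55 to 0.52 SD at r = 0.8). The gain is larger at lower r, and r is unknown.

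**Conclusion.** The point holds as one of precision and clarity. The between-group EEG test leaves the tested variable open and does not use the baseline EEG as a covariate. Compared with week 4 only, adjustment lowers the detectable difference from 0.86 SD to between 0.83 SD (r = 0.3) and 0.52 SD (r = 0.8). Compared with change, it lowers it from 1.02 to 0.83 SD at r = 0.3 and from 0.55 to 0.52 SD at r = 0.8. These figures assume 22 evaluable per arm, equal SDs at the two visits and a single uncorrected test. The correlation is an assumption, because the document gives none.

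The documents do not support a finding of bias or invalidity. The outcome is exploratory, so the primary COMI conclusion is unaffected. The change is worth making because it improves the comparison at almost no cost.

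**What to change.** In Statistical analysis, Neurophysiological outcome, replace the unpaired test with text to this effect:

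*Within each frequency band, week-4 normalised connectivity, voxelwise and per predefined region of interest, will be compared between arms by linear regression on arm, with the participant's baseline value at that voxel or region as covariate. Permutation inference will be used where the distribution requires it. The adjusted arm difference estimates the between-group difference in change from baseline to week 4.*

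The permutation scheme should be one that handles a covariate, and it should be named.

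The regression gives an adjusted arm difference, not a change value per participant. The correlations with the clinical variables should therefore keep a per-participant week-4 minus baseline change, stated as such.

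The cost is one degree of freedom per test and a slightly longer script. No data, visits or participants are added. Two predictors (arm and baseline) with 44 evaluable participants stay within the plan's own limit of one predictor per ten participants.
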